**FIG. 3. f3:**
[figure not shown]
Timeline of interventions and assessments. After the initial screening visit (S), each intervention consists of eight sessions of walking training (WALK) alone, followed by eight additional sessions of tAIH or Placebo before WALK_tSTIM_ or WALK_tSHAM_. Assessments occur at baseline (BL), at the end of intervention weeks 2 (T_0_), 3 (T_1_), and 4 (T_2_), and, again, after 1 (F_1_), 4 (F_4_), and 8 weeks (F_8_) after the last intervention session. tAIH, therapeutic intermittent hypoxia; WALK_tSTIM_, transcutaneous spinal stimulation-enhanced walking therapy.

We anticipate that tAIH before WALK_tSTIM_ will exceed the benefits of walking practice (WALK), tAIH + WALK_tSHAM_, or Placebo + WALK_tSTIM_ on enhancing the performance of the trained task of overground walking. Justification for the treatment sequence of tAIH followed by WALK_tSTIM_ is based on the estimated time (minutes) required for tAIH to facilitate expression of BDNF.^27^ Applying tAIH ∼1 h before WALK_tSTIM_ may promote temporal alignment of mechanisms of WALK_tSTIM_ neuromodulation with complementary mechanisms of tAIH-induced plasticity that involve BDNF. Details on these interventions are below.

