#### Gait

Overground walking ability is quantified by three primary measures: 10MWT (walking speed); TUG test (walking initiation and balance); and a 6MWT (walking endurance). These tests capture functional ambulation, exhibit high reliability and construct validity, and have precedence for quantifying and distinguishing degrees of functional ambulatory recovery post-SCI.^37–39^ Our previous study in persons with chronic SCI showed these tests to be more sensitive to changes in walking function and functional ambulation compared to American Spinal Injury Association Impairment Scale (AIS) grade or categorical ambulation metrics.^6,8^ During all walking assessments, we allow participants to use their least restrictive hand-held assistive device of choice.

Participants carry out two trials each for the 10MWT and TUG (at their fastest but comfortable and safe speed); the average speed will be used. A minimum of a 1-min rest between tests will be provided. Participants will perform the 6MWT only once at a walking speed sustainable for 6 min. The participant's walking distance at the 2- and 6-min mark will be recorded. We also record secondary outcome measures of walking function that include the Walking Index for Spinal Cord Injury (WISCI) II^40^ and SCI Functional Ambulation Index (SCI-FAI).^41^ To quantify strength, the AIS lower extremity motor scores (LEMSs) will be used.^42^

To quantify maladaptive changes that may occur subsequent to the combinatorial interventions, we measure pain, spasticity, systemic hypertension, AD, and cognitive ability during our assessments.

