### Statistical analysis

We plan to test three subhypotheses using parametric and non-parametric statistical inference methods. Statistical significance corresponds to a *p* value <0.05.

#### Hypothesis 1

Daily tAIH + WALK_tSTIM_ enhances overground walking ability in persons with chronic SCI compared to tAIH + WALK_tSHAM_ or Placebo + WALK_tSTIM_.

We predict a decrease in 10MWT and TUG time and an increase in 6MWT distance relative to baseline after tAIH + WALK_tSTIM_ (vs. Placebo + WALK_tSTIM_, tAIH + WALK_tSHAM_). We quantify walking ability using three outcome measures: change in TUG, 10MWT, and 6MWT relative to baseline assessments. Change in performance on these measures will occur after the last intervention session and again at 1-, 4-, and 12-week post-intervention follow-ups (Fig. 3). We will test three related subhypotheses using a linear mixed model with intervention (tAIH + WALK_tSTIM_, tAIH + WALK_tSHAM_, and Placebo + WALK_tSTIM_) and time (visit number) as the fixed main effects, with subject as random effect, whereas scores for TUG (time), 10MWT (time), and 6MWT (distance) will be considered as repeated measures.^56^

Differences from assessment after completion of the walking practice sessions will be compared between and within interventions at tests (T_1_, T_2_) and follow-ups (1, 4, and 8 weeks post-intervention). If analyses of variance (ANOVAs) reveal significant differences, the Tukey-Kramer *post hoc* test will identify pair-wise differences. If walking performance measures at the end of the walking practice sessions are significantly different between intervention groups, we will use an analysis of covariance. We also plan to fit a linear mixed model to test the magnitude and duration of tAIH priming effects based on linear contrasts after controlling for the study period, baseline primary outcomes, and demographics data.

#### Hypothesis 2

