### Study limitations

Clinical trials are necessary for the study of combinatorial interventions to treat SCI. However, the experimental protocols for these trials are often beset with study design challenges attributable, in part, to confounding treatment interactions, small sample size, short study duration, and SCI heterogeneity. The study of multiple treatments and their interactions requires the appropriate choice of controls to discriminate between the clinical outcome of the treatments alone, combined, or neither. Identifying the study groups is pivotal to trial success, but requires larger sample sizes. Because of challenges from the ethical perspective in SCI research with humans, we cannot include a control (no treatment) group in the present trial. We anticipate that some participants will receive additional therapy services upon study enrollment.

We will quantify the interactions between frequency/duration of these services and our primary outcome measures. The biostatistician also will use multi-variate statistical models to assess these and other potential confounds to our outcome measures. Though most studies continue for longer periods (e.g., 12 weeks),^61^ up to eight sessions of tAIH or WALK_tSTIM_ are sufficient to elicit improvements in walking speed in persons with SCI.^6,8,62^ To consider the potential long-term effects of tAIH + WALK_tSTIM_ on walking ability, we will follow up at 1, 4, and 8 weeks post-treatment.

Small sample sizes can undermine the translation of results to the larger heterogeneous patient population. We also acknowledge that balancing treatment groups of a heterogeneous SCI cohort will be a challenge. To address this obstacle, we will consider age, sex, reliance on walking aids,^63^ and injury level. Second, we do not yet know the potency of WALK_tSTIM_ and eight sessions may be considered too few to achieve MCID in the treatment groups. We chose eight sessions to remain pragmatic in treatment duration while aligning our study design to a recent placebo-controlled trial that found WALK_tSTIM_ induced clinically significant gains in walking speed within six sessions.^62^ We acknowledge that achieving MCID in eight sessions may not occur during treatments without tAIH. If this happens, we will compare groups using survival-type analyses to include those with no participants who achieved MCID.^64^ Third, medication changes are frequent in persons with SCI, which may alter neural plasticity.

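### Hypothesis 1 measures the primary walking outcomes from two different reference visits, baseline and the end of walking practice, and names a 12-week follow-up that is not scheduled

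*Protocol article*

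**What the plan says.** The Gait section sets the status of the outcomes: "Overground walking ability is quantified by three primary measures", namely the 10MWT, the TUG and the 6MWT.

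Statistical analysis, Hypothesis 1, then gives the reference visit twice:

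- The first paragraph defines the outcomes as "change in TUG, 10MWT, and 6MWT relative to baseline assessments".
- The second paragraph states: "Differences from assessment after completion of the walking practice sessions will be compared between and within interventions".

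The Figure 3 legend treats these as different visits: "Assessments occur at baseline (BL), at the end of intervention weeks 2" (T0), followed by T1, T2 and the follow-ups. The eight walking-practice sessions lie between BL and T0. Table 2 also codes baseline (B) separately from testing sessions (T). Under Randomization, participants are assigned in the order in which they finish walking practice, that is, around T0.

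The adjustment follows both lines as well. An analysis of covariance is used if the groups differ significantly at the end of walking practice, while the linear-contrast model is fitted after "controlling for the study period, baseline primary outcomes, and demographics data".

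For the last follow-up, the first paragraph says "again at 1-, 4-, and 12-week post-intervention follow-ups" and cites Figure 3. The Figure 3 legend says "8 weeks (F_8_) after the last intervention session", and Study limitations says "we will follow up at 1, 4, and 8 weeks post-treatment". The Table 2 footnote and the second paragraph of Hypothesis 1 also give 8 weeks.

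**The concern.** The quantity to be analysed for the primary outcomes is stated in two ways that cannot both hold. It is not a detail left to a fuller document, because the article states it twice.

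Three things depend on the answer. First, the plan includes within-intervention comparisons. Change from BL contains the effect of two weeks of practice given before assignment, so a gain in the tAIH + WALK_tSTIM arm would credit that practice to the combined treatment; change from T0 would not. Second, the two change scores have different variances in general, so they give different standard errors and, in one sample of about 16 completers per arm, different estimates and p-values. Third, with both versions on the page, the analyst can choose between them once the data are known.

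Hypothesis 2 is exposed to the same gap. It counts combined-treatment sessions needed to reach the MCID and adjusts for 10MWT speed at baseline, but does not say from which visit the MCID is measured.

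**Working it through.** **1. Side by side**

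| Item | Version A | Version B |
|---|---|---|
| Reference visit, primary outcomes | BL (Hypothesis 1, first paragraph) | T0 (Hypothesis 1, second paragraph) |
| Adjustment variable | baseline primary outcomes (contrast model) | end-of-practice value (ANCOVA, if groups differ there) |
| Last follow-up | 12 weeks (Hypothesis 1, first paragraph) | 8 weeks (second paragraph, Figure 3 legend, Table 2, Study limitations) |

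The third row can be resolved from the article: 12 weeks appears once, cites a figure that shows 8, and has no scheduled visit. The first two rows cannot. Reading baseline as T0 throughout would conflict with the Figure 3 legend and Table 2, which both reserve the word for the earlier visit.

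**2. What the anchor changes in expectation**

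Write Y_BL, Y_T0 and Y_t for the values at baseline, at the end of practice and at a later visit t. Then

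Y_t − Y_BL = (Y_t − Y_T0) + (Y_T0 − Y_BL).

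The last term is the practice change. It arises before any combined treatment, so under randomisation its expected value is the same in every arm.

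- Between arms: the term cancels in expectation, so both anchors target the same difference.
- Within an arm: the term stays, so change from BL equals change from T0 plus the practice gain.
- In a single sample of about 16 per arm: the observed practice change will not be exactly equal across arms, so the two analyses will give different numbers.

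**3. The plan's own power figure**

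Inputs from Sample size, Aim 1: SD of change in 10MWT time, stated relative to baseline, 3.0 s in tAIH + WALK_tSTIM and 2.0 s in the comparators; 16 completers per group; significance level 0.0167, taken as two-sided because the article does not say; differences of 5.2 s and 3.14 s.

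- Standard error = √(3.0²/16 + 2.0²/16) = √0.8125 = 0.901 s.
- Welch degrees of freedom = 0.8125² / [(0.5625² + 0.25²)/15] = 26.1.
- Noncentrality = 3.14/0.901 = 3.48 against tAIH + WALK_tSHAM, and 5.2/0.901 = 5.77 against Placebo + WALK_tSTIM.
- Power from the noncentral t = 81.5% and 99.9%.

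These agree with the stated >81% and >99%. Dropout also agrees: 16/(1 − 0.20) = 20 per group, 60 in total.

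**4. What that figure covers**

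The SDs are worded as change relative to baseline, so the 81.5% belongs to the BL version. The power of the T0 version depends on the SD of change from T0, which is not given and cannot be derived without between-visit correlations. As a sensitivity range for a 3.14 s difference, with a pooled t-test and a common SD in both arms, power is about 97% at SD 2.0, 82% at SD 2.55 (the root mean square of 3.0 and 2.0) and 66% at SD 3.0. Power is therefore sensitive to which change score is analysed, but the article does not show where the T0 version falls in this range.

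**The case against.** The strongest reply is that Hypothesis 1 is chiefly a between-group question, that both visits precede treatment, and that randomisation therefore makes the expected contrast identical from either anchor. That stands. The point is about within-group interpretation, precision and pre-specification, not about bias in the between-group comparison.

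A reader might infer a large loss of power: if the planning SDs described change from T0 and correlation decayed with lag from 0.8–0.9, the SD of change from BL would be 1.34–1.38 times as large, and power for 3.14 s would drop to about 50–52%. The article does not support this. It ties the SDs to baseline, so under the same assumptions, moving to T0 would raise power to about 98%. The result also depends on the decay assumed; with a constant correlation the ratio is 1 and nothing changes.

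A reader might also infer that participants could reach the MCID before the first combined session. That would follow only if the MCID were measured from BL. Hypothesis 2 uses baseline only for a covariate and names no reference visit for the MCID, so this is a possibility to close off, not a stated defect.

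Finally, it can fairly be said that the 12-week figure is an isolated slip. It is, but it sits in the outcome definition and miscites its own figure.

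**Conclusion.** The contradiction stands and needs no assumption: the primary outcomes have two reference visits, the adjustment has two matching covariates, and no other text settles the choice. The expected between-group difference is unaffected. The within-group comparisons, the precision and the realised result are affected, and a choice is left open after data are seen.

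No numerical loss can be attached to it. The sample-size arithmetic is sound (81.5% against the stated >81%, on a two-sided 0.0167 level with 16 per group) and describes change from baseline. The power of a T0-anchored analysis is not determined by the documents. The last follow-up is an error of one figure, not a genuine second horizon for durability.

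**What to change.** - In Hypothesis 1, name T0 as the single reference visit for the 10MWT, TUG and 6MWT, and as the covariate in both the ANCOVA and the contrast model. It is the last value before assignment and is already collected.
- In Hypothesis 2, state the same reference for the MCID session count, so that only change after walking practice is counted, and use the same visit for the speed covariate.
- Report the change from BL to T0 separately as the effect of walking practice.
- In Sample size, Aim 1, state which visit the SDs of 2.0 and 3.0 s refer to. If they remain baseline-based while the analysis uses T0, re-check that assumption.
- Replace the 12-week follow-up in Hypothesis 1 with the scheduled 8-week visit.

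The cost is a few wording edits and the check on the planning SDs. No new visit or measurement is needed. The edits should be made before unblinding.

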**FIG. 1. f1:**
[figure not shown]
Illustration of study hypotheses. We hypothesize that the combination of tAIH + WALK_tSTIM_ will result in larger, more persistent improvements (increase in efficacy) in walking speed than tAIH + WALK_tSHAM_ or Placebo + WALK_tSTIM_. Additionally, we hypothesize that tAIH + WALK_tSTIM_ will result in fewer training sessions to achieve an MCID in walking speed improvements (greater potency) compared to Placebo + WALK_tSTIM_ or tAIH + WALK_tSHAM_. MCID, minimal clinically important difference; tAIH, therapeutic intermittent hypoxia; WALK_tSTIM_, transcutaneous spinal stimulation-enhanced walking therapy.

These aims will be the first to investigate the safety and efficacy of tAIH priming with WALK_tSTIM_ to augment walking recovery in persons with chronic SCI. Determining how to harness these potentially synergistic treatments may lead to meaningful recovery that profoundly impacts the lives of persons with SCI while establishing more potent therapeutic strategies as a part of “best practices in SCI care.”

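### The Hypothesis 1 mixed model names only main effects of intervention and visit, so it cannot supply the visit-wise and duration comparisons that the same section promises

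*Protocol article*

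**What the plan says.** The Hypothesis 1 text under Statistical analysis contains three analysis statements.

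1. A linear mixed model for 10MWT, TUG and 6MWT, with intervention "and time (visit number) as the fixed main effects, with subject as random effect".
2. Visit-wise comparisons: differences from the end of walking practice "will be compared between and within interventions at tests (T_1_, T_2_) and follow-ups (1, 4, and 8 weeks post-intervention", with a follow-up procedure: "If analyses of variance (ANOVAs) reveal significant differences, the Tukey-Kramer *post hoc* test will identify pair-wise differences".
3. A further model: "We also plan to fit a linear mixed model to test the magnitude and duration of tAIH priming effects based on linear contrasts". The adjusters listed for it are period, the primary outcomes at baseline, and demographics.

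The target is set earlier. Hypothesis and aims makes lasting benefit the efficacy question of Aim 1, and the Fig. 1 legend says the combination "will result in larger, more persistent improvements (increase in efficacy) in walking speed" than either comparator.

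Neither model statement mentions an interaction between intervention and visit, and none appears elsewhere in the article.

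**The concern.** The first model is the only one whose intervention and visit effects are spelled out, and the form given does not fit its purpose. With main effects only, the arms are assumed to run parallel after walking practice: whatever separates them at T1 separates them by the same amount at week 8. Persistence is then an assumption of the model and cannot be a result of it.

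At stake is the central question of Aim 1 on the three primary walking measures. If the benefit fades, the additive estimate blends early and late visits and describes neither. If the term is added only after the data are seen, the choice will look data-driven.

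**Working it through.** **Step 1. What the stated model implies.** Write the expected change for arm a at visit k as μ + α_a + τ_k.

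- Arm difference at visit k: (μ + α_A + τ_k) − (μ + α_B + τ_k) = α_A − α_B, the same for every k.
- Arm difference in change from T2 to F8: (τ_F8 − τ_T2) − (τ_F8 − τ_T2) = 0, whatever the data.

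So neither an arm difference that varies by visit nor a test of differential persistence exists in this model. No numerical assumption is needed for that.

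The second model adjusts for study period, baseline outcomes and demographics. Fig. 3 shows one visit sequence for all arms. If study period means stage of that sequence, it is another τ term, and it cancels in the same way. A linear contrast of these parameters cannot express duration unless arm-by-visit parameters are present.

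**Step 2. The plan's own power figure.** Inputs from Sample size: differences -5.2 s and -3.14 s, SD 3.0 s in the combination arm and 2.0 s in each comparator arm, 16 completers per arm, alpha 0.0167 (two-sided assumed).

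- SE = √(9/16 + 4/16) = √(13/16) = 0.901 s.
- 3.14/0.901 = 3.48, Welch power 81.5%.
- 5.2/0.901 = 5.77, Welch power 99.9%.

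These match the stated >81% and >99%. They are power for a single two-arm comparison of change. They are not power for an all-visit average or for a persistence test.

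**Step 3. What the additive model would report if the effect fades.** Assumptions not in the documents: five visits (T1, T2, F1, F4, F8), balanced data, equal between-visit correlation ρ of 0.5 to 0.9, and the decay profile. In balanced data the main-effect contrast is the difference in subject means over visits.

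- Profile 100/100/50/0/0% of 3.14 s: 3.14 × (1 + 1 + 0.5 + 0 + 0)/5 = 1.57 s at every visit. The assumed truth is 3.14 s at T2 and 0 at F8.
- Variance factor for a mean of five visits: f = ρ + (1 − ρ)/5, which is 0.60 at ρ = 0.5 and 0.92 at ρ = 0.9.

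| Variance basis | SE, ρ = 0.5 / 0.9 | Significant at 0.05 | Significant at 0.0167 |
|---|---|---|---|
| Two compared arms, √(13f/16) | 0.698 / 0.865 s | 58% / 42% | 40% / 25% |
| Pooled over three arms, √(2 × 5.67 × f/16) | 0.652 / 0.807 s | 65% / 48% | 48% / 31% |

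Here 5.67 = (9 + 4 + 4)/3.

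**Step 4. Sensitivity to the profile.**

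- Leaving T1 out of the average: 3.14 × (1 + 0.5 + 0 + 0)/4 = 1.18 s.
- Linear waning to zero at F8 (100/100/67/33/0%): 3.14 × 3/5 = 1.88 s. By simulation with three-arm pooling and correlations 0.8 down to 0.3, this is significant at 0.05 in 65-90% of trials. With the interaction in the model, the F8 contrast rejects in about 7% (slightly above 5% because the arm SDs differ), and the T2-to-F8 arm contrast has 86-100% power.
- The same waning from 5.2 s: 5.2 × 3/5 = 3.12 s, significant in 97-100%.
- Build-up then decay (50/100/75/50/25%): 3.14 × 3/5 = 1.88 s. Power at 0.0167 is 37-56% for ρ of 0.9 down to 0.5 on the two-arm basis, against 81.5% for a single visit at full effect on the same basis.
- Constant 3.14 s: the additive model is unbiased and more precise than a single-visit contrast.

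**The case against.** The strongest reply is that the first model is not the whole Hypothesis 1 analysis. The section also plans comparisons at each test and follow-up, and a model "to test the magnitude and duration of tAIH priming effects based on linear contrasts". The authors plainly mean to examine persistence. This stands, and a reader should not infer that Aim 1 has no persistence analysis or is untestable.

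A reader might also infer that the trial will report a week-8 benefit that does not exist. The text does not support that. It nowhere says that the week-8 contrast is taken from the additive model, and a rejection from that model is a correct statement about the average over visits. The rates above apply only if visit-specific results are read from it.

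The term main effects may be loose wording. Hypothesis 3 uses nearly the same phrase beside a Friedman rank test, which has no such parameters, and a full SAP may name the interaction. That is possible. But this is a stated specification that conflicts with comparisons stated next to it, which is different from a detail left out, and it needs correcting whether the wording is loose or literal.

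The numbers depend on correlations and decay shapes that the documents do not give. That also stands; the constant-difference restriction does not depend on them. A worry that visit number might enter as a numeric trend is conjecture, and the ANOVA with Tukey-Kramer tests suggests categorical visits. Finally, which visits carry the lead contrasts is a choice of estimand for the investigators; any such choice needs the interaction.

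**Conclusion.** The concern holds in a limited form. The Hypothesis 1 model as written imposes one arm difference on all visits. It cannot produce the visit-wise or duration contrasts promised in the same section, or test the persistence hypothesised in Aim 1 and Fig. 1. The second model does not state the missing term.

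The size is conditional. For a 3.14 s effect on a 100/100/50/0/0% profile, the additive estimate is -1.57 s at every visit: half the assumed end-of-treatment effect, and 1.57 s where the assumed week-8 effect is zero. It would be significant at 0.05 in roughly 42-65% of trials for correlations of 0.9 down to 0.5, depending on the variance basis. Other profiles give other figures. Only an effect that is flat over all visits is represented correctly at each visit, and flatness is what Aim 1 sets out to examine.

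The algebra is certain. Whether the authors intended to exclude the interaction is not.

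**What to change.** In the Hypothesis 1 paragraph, state that visit is a categorical factor and add the intervention-by-visit interaction to the mixed model. Take the arm contrasts at each planned visit from that model, including the end of treatment (T2) and 8 weeks (F8). Test persistence as the arm difference in change from T2 to F8. Say whether the magnitude-and-duration model is this same model with covariates. Report the all-visit average as a summary only.

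The cost is one or two sentences before unblinding, with no new data or participants. With five visits and three arms, the interaction adds (3 − 1) × (5 − 1) = 8 parameters. The price is precision if the effect really is constant: the single-visit SE is 0.901 s, against 0.698-0.865 s for the average (ρ of 0.5 to 0.9). In simulation with a constant 3.14 s effect and three-arm pooling, power at 0.0167 was about 87-88% for the F8 contrast, against 92-99.8% for the average (correlations 0.8 down to 0.3).

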**FIG. 2. f2:**
[figure not shown]
Flow diagram of anticipated subject recruitment, enrollment, intervention allocation, and disposition status. We anticipate *N* = 48 people with SCI to complete the study. SCI, spinal cord injury; tAIH, therapeutic intermittent hypoxia; WALK_tSTIM_, transcutaneous spinal stimulation-enhanced walking therapy.

For Aim 1, our sample-size estimate focused on results from an earlier placebo-controlled clinical trial that reported that persons with incomplete SCI completed the 10-Meter Walk Test (10MWT) faster after tAIH + WALK (−4.3 ± 1.0 sec, faster relative to baseline) as compared to Placebo + WALK (0.9 ± 0.4 sec, slower relative to baseline).^6^ From these results, we conservatively estimated the standard deviation of the 10MWT time relative to baseline as 2.0 sec in Placebo + WALK_tSTIM_ and tAIH + WALK_tSHAM_ and 3.0 sec in tAIH + WALK_tSTIM_. The estimated difference between the change in tAIH + WALK_tSTIM_ and the change in Placebo + WALK_tSTIM_ was −5.2 sec, and that difference between tAIH + WALK_tSTIM_ versus tAIH + WALK_tSHAM_ was estimated as −3.14 sec. Assuming a 20% dropout rate with 16 completers per group, three outcome measures (10MWT, Timed Up and Go Test [TUG], and the 6-Minute Walk Test [6MWT]), and a significance level of 0.0167 adjusted for the three repeated outcomes,^20^ this study will have >99% statistical power in comparing tAIH + WALK_tSTIM_ versus Placebo + WALK_tSTIM_ and >81% statistical power in comparing tAIH + WALK_tSTIM_ versus tAIH + WALK_tSHAM_.

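### Applied literally, the Hypothesis 1 mixed model gives every visit one variance and one correlation, so the planned visit-wise comparisons would rest on a pooled error that may not fit any particular visit

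*Protocol article*

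**What the plan says.** In the protocol article, Statistical analysis, Hypothesis 1, the linear mixed model has intervention and "time (visit number) as the fixed main effects, with subject as random effect". The TUG, 10MWT and 6MWT scores "will be considered as repeated measures". Subject is the only random term named, and no residual covariance is given.

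The next paragraph goes visit by visit: "Differences from assessment after completion of the walking practice sessions will be compared between and within interventions at tests" T1 and T2 and at the 1-, 4- and 8-week follow-ups. ANOVAs with Tukey-Kramer pairwise comparisons follow. The same paragraph also plans to "fit a linear mixed model to test the magnitude and duration of tAIH priming effects based on linear contrasts"; its random effects and covariance are not stated.

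The Fig. 3 caption places the last assessment "8 weeks (F_8_) after the last intervention session". One sentence under Hypothesis 1 says 12 weeks instead. The 8-week timing is used here because the rest of the article uses it; the two should be reconciled.

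The Sample size section gives the only variability figures for the 10MWT change: "2.0 sec in Placebo + WALK_tSTIM_ and tAIH + WALK_tSHAM_ and 3.0 sec in tAIH + WALK_tSTIM". That is one SD per arm. No SD by visit and no correlation between visits appears anywhere.

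**The concern.** A random subject intercept with independent residuals is compound symmetry: the same variance at every visit and the same correlation between any two. The responses compared here are changes from T0, at visits spread unevenly from 1 to 10 weeks later. Changes over such different intervals need not be equally variable, and neighbouring visits often correlate more closely than distant ones.

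If the model is extended to give visit-wise contrasts and keeps this random part, each contrast takes its standard error from a variance averaged over all five visits. A visit with above-average variance then gets too small a standard error and too many false positives. A visit with below-average variance gets too large a standard error and loses power. Aim 1 concerns lasting gains, so the late visits carry much of its claim. The issue is separate from unequal variance between arms and from the absence of an intervention-by-visit term, and it would remain if both were dealt with.

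**Working it through.** **1. The plan's own figure.** Inputs from Sample size: 16 completers per arm, SDs 3.0 and 2.0 s, differences 5.2 and 3.14 s, alpha 0.0167 (taken as two-sided).
- Standard error = √(3.0²/16 + 2.0²/16) = √0.8125 = 0.901 s.
- Noncentrality = 5.2/0.901 = 5.77 and 3.14/0.901 = 3.48.
- Noncentral t power = 99.9% for the first comparison, and 82.2% (30 df) or 81.5% (Welch) for the second.

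The stated >99% and >81% reproduce. They come from a single two-sample comparison and do not depend on the covariance across visits.

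**2. Visit spacing.** From the Fig. 3 caption, T0, T1 and T2 fall at the end of intervention weeks 2, 3 and 4, and the follow-ups 1, 4 and 8 weeks after the last session. Weeks after T0 are therefore T1 = 1, T2 = 2, F1 = 2+1 = 3, F4 = 2+4 = 6 and F8 = 2+8 = 10.

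**3. What the pooled error does.** With complete data, an arm-by-visit mean and a random intercept, the model variance at each visit is the mean of the five visit variances. Hence
- ratio at visit j = model SE / true SE = √(mean variance / variance at j);
- large-sample type I error at nominal 5% = 2[1 − Φ(1.96 × ratio)].

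The arm effect averaged over visits uses the between-subject mean square, which estimates the right quantity; its type I error stays at about 5%.

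**4. If correlation decays with time (assumed).** Let the stable part of the score have correlation exp(−lag/τ), and let r be the SD of measurement noise relative to it. In units of the stable variance, the change from T0 at week t has variance 2(1 − e^(−t/τ)) + 2r².

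Worked case, τ = 12 weeks, r = 0.5:
- variances at T1, T2, F1, F4, F8 = 0.660, 0.807, 0.942, 1.287, 1.631; mean 1.065;
- F8 ratio = √(1.065/1.631) = 0.808, type I error 11.3%;
- T2 ratio = √(1.065/0.807) = 1.149, so the standard error is 15% too wide and type I error is 2.4%.

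Over τ = 3, 6, 12, 24 weeks and r = 0.25, 0.5, 1:

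| Quantity | Range |
|---|---|
| F8 type I error, nominal 5% | 6.8–14.6% |
| F8 type I error, nominal 1.67% | 2.6–7.6% |
| T2 standard error too wide by | 4–26% |
| T1 type I error, nominal 5% | 0.2–3.9% |

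Simulation with 16 per arm (8,000 runs per setting) gave 7–15% at F8, against 5% with visit-specific variances.

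**5. Other variance patterns (also assumed).** The same formula, with the SD changing by a factor of 1.25 to 2:

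| Pattern of SD over visits | T2 type I error | F8 type I error |
|---|---|---|
| Equal | 5% | 5% |
| Rising from T1 to F8 | 3.6% to 1.2% | 8.5% to 16.3% |
| Falling from T1 to F8 | 5.9% to 7.3% | 3.1% to 0.5% |
| Peaking at T2 | 8.3% to 15.6% | 3.0% to 0.5% |

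**6. Raw scores as the response.** Under the step 4 assumptions, comparing arms on the score at a single visit keeps 5% at T2 and F8. The T0-to-visit differences that the plan names do not: 6.8–14.4% at F8, with the T2 standard error 4–27% too wide.

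**The case against.** The strongest reply is that the article does not exclude a residual covariance. It never says that subject is the only covariance term, it calls the scores repeated measures, and it may leave the structure to an analysis plan that is not shown. This stands in part, and is why the point is conditional on a literal reading. But the random part is named in print, and an analysis plan that follows it would inherit the restriction. Labelling scores as repeated measures names no structure.

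Second, the model has main effects only, so it yields one averaged arm effect, which is sound. That is correct for that effect, but the plan also promises comparisons at each visit, and those need an error term.

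Third, the visit-wise ANOVAs might be run separately per visit, which would use visit-specific variances, and duration is assigned to a second mixed model. If so, the visit-wise tests escape the problem. The text does not say this, and the second model states no covariance.

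Fourth, a reader might infer that error bars are definitely too narrow at 8 weeks and too wide at the end of treatment. The documents do not support that. They give no visit-level variance or correlation, and step 5 shows that the direction can vanish or reverse. A response that varies most at T2 and then fades is not far-fetched.

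A reader might also extend the point to a T2-to-F8 loss-of-effect test. The plan names no such contrast.

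**Conclusion.** The point holds conditionally. If subject is the whole of the covariance model, the planned comparisons of change from T0 at T1, T2, F1, F4 and F8 have incorrect standard errors unless variances and correlations are truly equal across visits. Under decaying correlation, with the assumed ranges in step 4, the size is about 7–15% false positives at 8 weeks for a nominal 5% test and a T2 standard error about 4–26% too wide. Under falling or T2-peaked variance, the excess moves to T2 (5.9–15.6%) and the 8-week test becomes conservative (3.1–0.5%). None of these figures can be derived from the documents alone. The need for a change does not depend on the direction, since only equal variances and correlations leave every visit-wise test sound.

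It would be wrong to conclude that the trial's power statement is in error or that the overall arm effect is compromised: the stated power reproduces, and the averaged effect keeps its 5% level.

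**What to change.** For the visit-wise and duration contrasts, replace the random subject effect by an unstructured covariance over T1, T2, F1, F4 and F8, with visit as a categorical factor and Kenward-Roger degrees of freedom. Prespecify a heterogeneous-variance structure based on actual weeks for use if the unstructured model does not converge. State that these contrasts are taken from this model.

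The cost is one sentence and no new data. Five visits require 5 × 6/2 = 15 covariance parameters from about 48 completers (3 × 16), with slightly fewer degrees of freedom. In return, the contrasts do not depend on guessing how variance moves between visits.
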